#### Waiting list protocol

The control group will be in the 6 weeks waiting list without getting additional ADHD treatment. In the first visit at week 3 and at week 6, a life-style education for parents will be conducted with an ADHD symptom improvement check. A CGI-I score ≥6, is a cue for the participant to stop waiting and drop-out (then, the same as in the acupuncture treatment group for study ethical issues). After the waiting endpoint, participants will similarly be given acupuncture treatment for 6 weeks without an additional life-style education for parents.

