### Participants

Parents were initially screened by phone, and their children were included in the study if the inclusion criteria were met. The inclusion criteria includes being between 7-18 years of age, having a diagnosis of ADHD (any subtype) according to Diagnostic and Statistical Manual of Mental Disorders (DSM-IV) criteria and having an informed verbal and written consent from parents and participants. It did not matter whichever intervention (pharmacological, psychosocial therapy, educational, or occupational therapy, as examples) was used, if there were not any change of ADHD treatments/symptoms for the past 2 weeks. Exclusion criteria are a diagnosis of a developmental disorder, past history of epilepsy, the presence of another neurotic disorder, pregnancy, and any changes in medications during the course of the study. During waitlist period, a CGI-I score ≥6, is a cue for the participant to stop waiting and to drop-out.

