### Measures

DSM-IV ADHD diagnostic criteria [1,37] were used by the principal investigator to establish a diagnosis. Once randomised, participants were evaluated by the principal investigator during study visits at baseline and weeks 3 and 6 (or 3, 6, 9, and 12). The reliable and validated Korean version of the ADHD rating scale (K-ADHD-RS) [38] was used pre- and post-intervention as a primary outcome measure.

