### Primary outcome measures

The primary outcomes for the study were changes in ADHD symptoms from baseline to week 6 (or from week 6-12) as measured by the K-ADHD-RS [38]. The K-ADHD-RS is an 18-item standardized, valid, reliable instrument for the diagnosis and also a weekly assessment tool for checking the of treatment response among children and adolescents with ADHD [39]. Each item on the instrument describes one of the symptoms of ADHD rated on a 0-3 point Likert scale (0 = never or rarely, 1 = sometimes, 2 = often, and 3 = very often) [39]. The principal investigator administered the K-ADHD-RS to the parent at each study visit. Nationally representative norms are available for the scale and were used to determine eligibility [39].

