### Randomization and treatment allocation

This study is designed as a waitlist controlled open trial. Eligible participants were randomly allocated to one of two groups: group A (acupuncture) and group W (waitlist). In each group, participants were stratified according to the pharmacologic intervention at the initiation of the study. A computer generated randomization scheme was used. The principal investigator generated the random allocation sequences without any notice to sub-investigators. Stratified randomization was performed as a separate randomization procedure within each of two subsets of participants (without pharmacologic intervention, 1-60; with pharmacologic intervention, D1-D40. Other treatments were not concerned.) by using block size "4". Each number and its randomised letter (A or W) were placed in an opaque envelope. Each envelope was numbered consecutively from 1-60 and D1-D40. As each parent called to have their child screened, they were allocated the next consecutive number once they were eligible, so that for each eligible participant, no. 1 was allocated to envelope no. 1, etc. The screener was unaware of the sequence of group allocation at the time of screening phase. Hence, allocation was concealed at the time of recruiting.

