### Protocol

Group A (acupuncture group) continued with their existing program and the acupuncture protocol was added to their regimen. Group W (waitlist group) continued with their existing program and the waitlist protocol was added to their regimen. The participants in group A attended a clinical facility for the first 6 weeks and received 12 treatments (two times per week) for approximately 20 minutes. During this first 6-week period, group W consisted of children who continued with their existing ADHD treatment regimen as prescribed by their pediatrician, clinical psychologist and/or medical doctor. Then, the participants in group W were scheduled for another 12 treatments over the next 6 weeks (same as group A, two times per week).

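### A waitlist child rated much worse at week 3 by an unblinded rater becomes a drop-out, so the week-6 primary score is lost or taken after early acupuncture

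*Protocol article*

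**What the plan says.** The exit rule appears twice in the protocol article. Waiting list protocol: "A CGI-I score ≥6, is a cue for the participant to stop waiting and drop-out". Participants: "During waitlist period, a CGI-I score ≥6, is a cue for the participant to stop waiting and to drop-out". The first is followed by a bracket, "then, the same as in the acupuncture treatment group for study ethical issues", which most naturally means that the child moves on to acupuncture. The acupuncture protocol section has no matching rule for group A.

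Under Secondary outcomes, CGI-I is rated at weeks 3 and 6 (also 9 and 12 where applicable); 6 means much worse and 7 very much worse. The rater knows the arm. Under Measures, "participants were evaluated by the principal investigator during study visits at baseline and weeks 3 and 6"; under Randomization and treatment allocation, "The principal investigator generated the random allocation sequences without any notice to sub-investigators". The Discussion concedes that assessment was not blinded.

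The primary outcome is K-ADHD-RS change from baseline to week 6, and "The principal investigator administered the K-ADHD-RS to the parent at each study visit". After the waiting period, "the participants in group W were scheduled for another 12 treatments over the next 6 weeks". The Analysis section plans intention-to-treat (ITT) on the 3-week and 6-week K-ADHD-RS data.

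**The concern.** The rule ends control follow-up because of the outcome. Only children who are doing badly leave, they leave the waitlist arm, and an unblinded global rating decides who leaves. What is lost is the untreated week-6 value of the worst controls, which belongs in the primary comparison.

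This is a rule of conduct and not an analysis detail. The sample size section treats drop-outs as lost from the 32 evaluable children per group, so a child given that label would ordinarily have no week-6 score. If the child is treated and scored anyway, the score reflects early acupuncture. No later analysis can recover an untreated value that was never taken.

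The direction of the bias depends on handling. Omitting the child, or scoring after early acupuncture, pulls the difference toward no effect. Carrying the week-3 score forward mostly inflates it.

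**Working it through.** **Inputs from the article.** Difference 7.04, SD 9.9 in both groups, two-sided 5%, 80% power, 32 evaluable per group, 20% dropout, 80 in total (Sample size justification); 40 per arm (Design).

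**The plan's own figure.** n = 2(1.960 + 0.842)² × 9.9² / 7.04² = 2 × 7.85 × 98.01 / 49.56 = 31.0, taken as 32 per group. The t-test power at 32 is 0.800. 32 / 0.80 = 40 per arm, 80 in total. The figure reproduces.

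**Which visit matters.** A child triggered at week 6 is scored at that visit and is then due for acupuncture anyway. Only a week-3 trigger affects the primary outcome. Such a child should have a week-3 K-ADHD-RS.

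**Assumptions.** The article gives no trigger rate.
- Share of group W triggered at week 3: p = 2.5%, 5%, 10% (1, 2, 4 of 40).
- Waitlist changes are normal with SD 9.9. The week-3/week-6 correlation r36 is 0.5–0.7.
- The trigger correlates r1 = 0.6–1.0 with week-3 change.
- pc is the partial correlation of the trigger with week 6 given week 3: 0, 0.2 or 0.4 (above 0 only for r1 of 0.6–0.8).
- Trigger/week-6 correlation: ρ = r1·r36 + √(1−r1²)·√(1−r36²)·pc.
- Normal density at the cut: φ(1.960) = 0.0584 for 2.5%, φ(1.282) = 0.1755 for 10%.

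**(a) Week 6 predicted from week 3.** Simulation of 4 million controls: regress week 6 on week 3 in untriggered children and predict the triggered. With pc = 0 the bias is within 0.001 points everywhere. With pc = 0.2–0.4 the effect is understated:

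| Triggered | Understatement (points) |
|---|---|
| 2.5% | 0.06–0.17 |
| 5% | 0.11–0.32 |
| 10% | 0.20–0.60 |

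Worst-case power at 32 per group is 0.727. In 20,000 simulated trials with 40 per arm, 4 triggered, r1 = 0.8 and r36 = 0.6, full data gave a mean of 7.03 (SE 2.23). The model gave 7.03 (SE 2.28) at pc = 0, 6.80 at pc = 0.2 and 6.62 at pc = 0.4.

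**(b) Scored at week 6 after early acupuncture.** Dilution = p × f × 7.04, where f is the share of the effect reached. With f = 0.5:

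| Triggered | Dilution (points) | Power at 32 per group |
|---|---|---|
| 2.5% | 0.09 | 0.790 |
| 5% | 0.18 | 0.779 |
| 10% | 0.35 | 0.758 |

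Over f = 0.25 to 1 the range is 0.025 × 0.25 × 7.04 = 0.04 to 0.10 × 1 × 7.04 = 0.70.

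**(c) Week 3 carried forward.** Shift = 9.9 × φ × (r1 − ρ); positive inflates the effect.
- Lowest (p = 10%, r1 = 0.6, r36 = 0.7, pc = 0.4): ρ = 0.42 + 0.8 × 0.714 × 0.4 = 0.648; 9.9 × 0.1755 × (0.600 − 0.648) = −0.08.
- Highest (p = 10%, r1 = 1, r36 = 0.5): 9.9 × 0.1755 × 0.5 = +0.87.

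**(d) Omitted.** Shrinkage = 9.9 × ρ × φ / (1 − p).
- Lowest (p = 2.5%, ρ = 0.6 × 0.5 = 0.30): 9.9 × 0.30 × 0.0584 / 0.975 = 0.18; power at 32 per group 0.779.
- Highest (p = 10%, ρ = 0.8 × 0.7 + 0.6 × 0.714 × 0.4 = 0.731): 9.9 × 0.731 × 0.1755 / 0.90 = 1.41; power 0.610.

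Omission does not fit the stated ITT, so (d) is an outer bound.

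**Scale.** SE at 40 per arm = 9.9 × √(2/40) = 2.21. The worst case of (a) is 0.60 / 2.21 = 0.27 SE; of (d), 1.41 / 2.21 = 0.64 SE.

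**The case against.** The strongest defence is that the article never says assessment stops. Measures lists week-3 and week-6 evaluation without exception, and the stated ITT anticipates children who do not complete. If the bracket means the child moves to acupuncture, that child still attends the clinic and could be rated, and the remaining defect is the word drop-out. This is a fair reading, but the text does not secure it. The article labels the child a drop-out twice, and its sample size treats drop-outs as not evaluable. The score, if taken, would still follow acupuncture.

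The bracket might instead extend the rule to group A. Tying the rule to waiting argues against that. Even if it did, week-6 scores would still be lost selectively.

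The size objection largely stands. Entry is allowed only "if there were not any change of ADHD treatments/symptoms for the past 2 weeks", so very few children may become much worse within three weeks. The +0.87 also requires carry-forward, which the article does not state, and a trigger identical to the week-3 score. The calculations contain no arm-dependent rating bias, so the effect of the unblinded rater is not quantified.

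It is also true that scoring after early acupuncture dilutes the ITT estimate. If exit depends only on the week-3 score, a model using that score is nearer the untreated contrast. The gain from the fix is an estimate that matches the stated ITT and does not rest on that assumption; a smaller bias in every scenario is not claimed.

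**Conclusion.** The concern holds, as something that should be fixed and not as a fatal flaw; confidence is medium. Followed as written, the rule selectively loses or contaminates the week-6 score of deteriorating controls. With the recorded week-3 score in a model, almost all of the bias goes if exit depends only on that score. Because the trigger is a separate, unblinded global rating that may say more about week 6, this is not assured.

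The sizes rest on an assumed trigger rate, normal changes and assumed correlations. If no child is triggered at week 3, nothing is lost.

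**What to change.** Keep the clinical rescue. Replace the drop-out wording in Participants and Waiting list protocol, and the bracket, with these points:

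1. A waitlist child with CGI-I of 6 or more stops waiting and may start acupuncture, but stays in the study.
2. The scheduled week-3 K-ADHD-RS is recorded before any acupuncture.
3. The child is still scored at week 6 from randomisation and analysed in group W under the stated ITT.
4. One sensitivity analysis sets aside scores taken after early acupuncture and predicts week 6 from the week-3 score.

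The cost is two or three sentences, one extra week-6 rating per triggered child (1–4 children under the assumptions) and one further analysis. The downside is the dilution in (b), which the sensitivity analysis sets in context. The sample size of 80 is unchanged, and the article describes recruitment as still under way.

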### Risks

One of the advantages of acupuncture is that the incidence of adverse effects is substantially lower than that of many drugs used for the same conditions [59]. In a review by Ernst [60], the most common reported adverse effects were pain (1-45%), fatigue (2-41%), and bleeding (0.03-38%). Although these are rare [61,62], acupuncture is associated with life-threatening complications that include pneumothorax, angina pectoris, septic sacroilitis, epidural abscess, and temporomandibular abscess [63]. For an accurate observation of acupuncture adverse effects, we made an "Adverse Events Report" at every visit.

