## Abstract

**Background:**

Attention-deficit/hyperactivity disorder (ADHD) is a common neuro-psychiatric problem, affecting 7-9% of children. Pharmacological interventions are widely used with behavioral treatments in ADHD. Still, the origin of ADHD is unclear, limiting pharmacological effectiveness and making adverse effects common. The use of complementary and alternative medicine (CAM) has increased, especially for developmental and behavioral disorders, such as ADHD. CAM is used by 60-65% of parents of children with ADHD to relieve ADHD-associated symptoms and to avoid the side effects of conventional medication. Acupuncture has been widely used to treat patients with ADHD, but the available evidence of its effectiveness is insufficient. Our aim was to evaluate the effectiveness and safety of acupuncture in patients (both and each treatment naive and conventional therapy children) with ADHD (any subtype) compared to the waitlist control.

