**Methods/Design:**

This study is a waitlist controlled open trial. We used a computer generated randomization scheme. This randomised, controlled trial had two parallel arms (acupuncture, and waitlist group). Each arm consisted of 40 participants. The acupuncture group received acupuncture treatment two times per week for a total of 12 sessions over 6 weeks. Post-treatment follow-up was performed 3 weeks later to complement the 12 acupuncture sessions. Participants in the waitlist group did not receive acupuncture treatments during the first six weeks but were only required to be assessed. After 6 weeks, the same treatments given to the acupuncture group were provided to the waitlist group. The primary outcome of this trial included differences in Korean version of ADHD-Rating Scale (K-ADHD-RS) before randomization, 3 weeks and 6 weeks after randomization, and 3 weeks after completing the treatment.

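### Adverse-event reports follow visits (12 versus 2 in weeks 0-6), so any safety comparison with the waitlist is open to unequal ascertainment; abstract and Objectives differ on whether one is intended

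*Protocol article*

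**What the plan says.** The Risks section gives the only collection rule: "we made an 'Adverse Events Report' at every visit". It sets no separate rule for either arm.

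Visit frequency in weeks 0-6 differs by arm. The abstract's Methods give the acupuncture group treatment "two times per week for a total of 12 sessions over 6 weeks". Under the Waiting list protocol, the control group's contacts after baseline are these: "In the first visit at week 3 and at week 6, a life-style education for parents will be conducted". The Measures section agrees, with assessments at baseline and at weeks 3 and 6.

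The safety aim appears in two forms. The abstract's Background says "Our aim was to evaluate the effectiveness and safety of acupuncture in patients", and the same sentence ends "with ADHD (any subtype) compared to the waitlist control", so the waitlist serves as comparator for both aims. The Objectives section attaches the waitlist to effectiveness only and lists safety as a second aim without a comparator. The Analysis section plans group comparisons for the primary and secondary outcome measures. It does not name adverse events, and they are not among those measures.

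**The concern.** When an event is recorded only if somebody asks, the number found depends on how often the question is put and how far back it reaches. Here the number of occasions differs between arms by design. Two of the three common effects listed under Risks, pain and fatigue, also occur in untreated children. Separating that background from an effect of needling is the one thing a waitlist comparison of safety could offer. If the acupuncture group is asked twice a week and the waitlist group every three weeks, an excess in the acupuncture group could be a true effect, a result of asking more often, or both. The data would not tell these apart. Analysis cannot repair this later, because complaints that waitlist families had forgotten by weeks 3 and 6 were never recorded.

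**Working it through.** The article states no adverse-event rate and no adverse-event test, so there is no figure of its own to reproduce on this point. Its sample size calculation concerns K-ADHD-RS and has no bearing here.

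**Inputs from the article**
- Acupuncture group, weeks 0-6: 2 visits per week × 6 weeks = 12 (abstract, Methods; Protocol).
- Waitlist group, weeks 0-6 after baseline: 2 visits, at weeks 3 and 6 (Measures; Waiting list protocol).
- 40 children per arm (Design).

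**Contact ratio.** 12 / 2 = 6.0. If a separate baseline visit is counted in both arms, 13 / 3 = 4.3.

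**Assumptions (not in the article)**
- Acupuncture has no effect on general complaints.
- In each half-week a child has, independently, a probability p of a complaint that would be reported if asked about within the recall window.
- Treatment visits are half a week apart, so the acupuncture group's reports cover all 12 half-weeks.
- Each waitlist visit captures the last L weeks, up to 3. Two visits then cover m = 2 × 2L = 4L half-weeks.

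**Formulas.** Share of children with at least one recorded event:
- acupuncture: 1 − (1 − p)^12
- waitlist: 1 − (1 − p)^m
- ratio of observed time: 12 / m

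**Results at p = 0.05.** Acupuncture: 1 − 0.95^12 = 46.0%, or 40 × 0.460 = 18.4 children.

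| Waitlist recall L | m | Observed-time ratio | Waitlist share | Waitlist children of 40 |
|---|---|---|---|---|
| half a week | 2 | 6.0 | 1 − 0.95^2 = 9.8% | 3.9 |
| 1 week | 4 | 3.0 | 1 − 0.95^4 = 18.5% | 7.4 |
| 2 weeks | 8 | 1.5 | 1 − 0.95^8 = 33.7% | 13.5 |
| 3 weeks (full) | 12 | 1.0 | 1 − 0.95^12 = 46.0% | 18.4 |

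**Other values of p, at the half-week extreme.** p = 0.02 gives 21.5% versus 4.0%; p = 0.10 gives 71.8% versus 19.0%. With full three-week recall the arms are equal at every p.

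So p sets the level of reporting, but recall decides whether there is a gap at all. In observed time, the false excess runs from none to six-fold.

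**After the fix.** With only the contacts common to both arms, the ratio is 2 / 2 = 1.0, and both arms look back over the same three weeks.

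**The case against.** The strongest reply is that the article does not commit to this comparison. The formal Objectives give safety no comparator, Risks describes the report as a means of observing effects of acupuncture, and the Analysis section plans no adverse-event contrast. Its general remark that every analysis is performed among the two groups does not mention adverse events. This stands in large part: the comparison rests on one sentence of the abstract. That sentence is still a published aim, and it does not match the Objectives.

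Second, the report may cover everything since the previous visit. The look-back and wording would normally sit in the case record form or full protocol, neither of which is shown. This also stands. Their absence from an article is no fault, and with complete recall the arms do not differ. What the article does fix is reporting tied to visits, with 12 visits against 2. Full recall of minor fatigue over three weeks is the favourable end of the range.

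Third, the consequence is limited. Bleeding or pain from needling cannot arise in children who are not needled, so attributing those events needs no control group. The bias would exaggerate harm, not hide it, and K-ADHD-RS is untouched. All of this is correct. It confines the point to general complaints, where a false excess would still misinform parents.

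A reader might go further and infer that the trial's safety comparison is biased about six-fold. The documents do not support that. Six is the ratio of visits, and it becomes the ratio of observed time only if waitlist families recall no more than the last half-week.

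**Conclusion.** The point holds in limited form. The abstract and the Objectives need to agree on whether safety is compared with the waitlist. If it is, a comparison of all visit reports in weeks 0-6 is open to unequal ascertainment of general complaints, in the direction of overstating harm from acupuncture. At an assumed p of 0.05 per half-week and no true effect, the gap runs from 46.0% versus 9.8% (half-week recall) to none (full three-week recall). Both p and the recall window are assumptions, and the article does not say where the trial falls in that range. It would be wrong to say that the rule must produce an excess, or that some excess must remain whatever the recall. The change is worth making because it is cheap and because events that were not asked about cannot be recovered.

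**What to change.** 1. State the same safety aim in the abstract and the Objectives: either compared with the waitlist, or descriptive in treated children only.
2. If arms are compared, restrict the comparison for weeks 0-6 to the week 3 and week 6 assessments. Use the same question in both arms, covering the whole interval since the last assessment. Ask it afresh in the acupuncture group rather than filling it in from treatment-visit reports.
3. Keep recording events at every treatment visit. Report them separately as descriptive rates per session (acupuncture group weeks 0-6, waitlist group weeks 6-12), with no contrast against the waiting period.

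The cost is a sentence or two in the Risks and Objectives text and one extra table. The small downside is that the between-arm table will not contain every event recorded in the acupuncture group; the per-session table will hold the rest. Equal enquiry does not remove differences in reporting that come from families knowing their allocation in an open trial, and the report should say so.

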### Ethics review and informed consent

The trial protocol was reviewed by the Kyung-Hee Korean Medical Center Institutional Review Board. We prepared two types of consent forms, one for participants who are 7-13-years-of-age (explained in easier words) and another for those who are 14-18-years-of-age. For 7-13-year-old participants, a "comprehension check form" is used to confirm their full understanding. All children participants make their own decisions about participation in a clinical trial. All parents of the participants are issued with duplicate copies of the informed consent forms, with the original copies kept by the hospital. The informed consent form conveys the following information: names of the chief investigator and supervisors; the name of the hospital and the department conducting the research, a brief description of the control and treatment groups, the duration of the study, the questionnaires used, the Ethics approval, the right to withdraw their child at any time, and the fact that the results of the study will be disseminated via conferences and publications while maintaining the child's privacy.

